### Secondary outcome measures

#### Functional status

The Functional Activities Questionnaire (FAQ) [55] and Quality of Life after Brain Injury Overall Scale (QOLIBRI-OS) [56] will be used to assess functional status. The FAQ is a 10-item questionnaire measuring a person’s ability to perform daily tasks such as writing checks, shopping, preparing meals, and others [13, 55]. Items on the FAQ are scored using a 4-point Likert scale ranging from 0 (normal) to 3 (dependent). The FAQ has excellent inter-rater reliability and is highly correlated with other instrumental activities of daily living (IADL) measures such as the Lawton and Brody’s IADL [55]. The QOLIBRI-OS is a brief 6-item measure that assesses overall satisfaction with physical condition, cognition, emotions, function, personal/social life, and current situation/future prospects in people with TBI [56]. Items on the QOLIBRI-OS are scored using a 5-point Likert ranging from 1 (not at all) to 5 (very). Scores are summed and converted to a percentage where 0 % represents the lowest and 100 % the highest possible health-related quality of life. The QOLIBRI-OS is a unidimensional scale that demonstrates good reliability and correlates highly with the full 37-item QOLIBRI scale and other measures of health-related function [56].

#### Psychological health

The 9-item Patient Health Questionnaire (PHQ-9) will assess depressive symptoms with items scored using a 4-point Likert scale from 0 (not at all) to 3 (nearly every day) [57]. Total scores on the PHQ-9 can range from 0 to 27. Scores of 10 or greater are commonly used cutoff points for clinically significant depressive symptoms [58]. In a psychometric study of the PHQ-9 in persons with TBI, the instrument demonstrated acceptable test-retest reliability and is a sensitive and specific measure when compared to a diagnosis of major depression [59]. The PTSD Checklist-Civilian Version (PCL-C) is a 17-item questionnaire that will be used to measure PTSD symptoms [60]. Patients rate questions about how much they are bothered by particular symptoms during the past month using a 5-point Likert scale from 1 (not at all) to 5 (extremely). The PCL-C has demonstrated acceptable test-retest reliability and internal consistency values, and good convergent validity with moderate to high correlations with other PTSD instruments and measures of anxiety and depression in patients with traumatic injury [61]. Studies have also found that trauma survivors with PCL-C scores equal to or greater than 45 have a 75 % probability of developing symptoms consistent with a diagnosis of PTSD [62, 63].

### Sample size

We estimated power based on a target of 90 participants (30 per group) with complete follow-up data on 72 (85 %) by the 7-month follow-up. Power was estimated by generating simulated data, and then using simulated data to try and estimate the original model parameters. Simulated datasets were generated from available pilot data. Control subjects were resampled from control individuals in the pilot data, and treatment subjects were also resampled from control individuals, but with the target effect size added to the sampled values. Power was estimated by fitting Bayesian models to each of the simulated datasets for each response variable and recording the proportion of calculated 95 % credible intervals for effect sizes that excluded zero. There will be sufficient power to detect the following effect sizes: 2.0 points on the D-KEFS Tower test, 10.0 points on the Trails B and FAS tests, 4.0 and 6.0 points on the DEX and CFQ instruments, respectively, and minimum detectable differences of 23 % for depressive symptoms and 19 % for PTSD symptoms.

### Data analysis

All data will be explored numerically and graphically for normality and appropriateness of parametric statistical testing. Analyses will be conducted using models with either original data or suitably transformed data (for example, log-linear transformation) or nonparametric analyses if necessary. Baseline variables will be summarized using appropriate descriptive statistics and compared across groups. The characteristics of the patients who are lost to follow-up will be compared to those who complete the follow-up assessments. For each outcome, we will perform longitudinal mixed-effects regression analyses, with a random intercept for patient to account for the correlation among observations from the same patient. We will examine possible nonlinear effects of the treatment over time. A random slope over time may be included to allow a separate slope to be estimated for each patient. We will fit the model with an independent conditional covariance structure and an autoregressive structure and choose the best data-supported model based on the deviance information criteria or a related criterion. The primary analysis will be intent-to-treat; missing observations due to dropout and other reasons not related to the treatments will be handled with multiple imputation methodology [64]. Statistical significance will be *P* <0.05. All analyses and reporting will be consistent with Consolidated Standards of Reporting Trials (CONSORT) guidelines. The data analysis plan will be fully specified and approved prior to completion of data collection.

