## Methods/design

### Study design

This study is a three-group randomized controlled trial conducted at a Level I trauma center. Figure 1 depicts the overall study design with assessments at 6 weeks (baseline) and 4 and 7 months after hospital discharge (see ClinicalTrials.gov and NCT01714531 for more information). The investigators, participating surgeons, research personnel conducting the assessments, and patients will be blinded to group assignment. Potential subjects will be informed that they will be randomly assigned to one of two different educational treatments or usual care. Participants will be asked not to discuss study procedures with their treating surgeon, medical staff, and research personnel.

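### Unless a random slope is added, both covariance candidates assume equal spread at all three visits, so the 7-month standard error is off if spread changes; an unstructured 3×3 covariance is a cheap improvement

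*Protocol article*

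**What the plan says.** The protocol's Data analysis section specifies, for every outcome, "longitudinal mixed-effects regression analyses, with a random intercept for patient to account for the correlation among observations from the same patient". It then adds an option: "A random slope over time may be included to allow a separate slope to be estimated for each patient". No rule says when the slope enters. The residual structure is settled by the data: "We will fit the model with an independent conditional covariance structure and an autoregressive structure and choose the best data-supported model". The yardstick for that choice is the DIC or a similar measure. The residual structures are conditional, that is, they apply given the random effects. The text does not say whether the autoregressive structure has equal variances, and it lists no unstructured or visit-specific-variance candidate. The same section allows "models with either original data or suitably transformed data (for example, log-linear transformation) or nonparametric analyses if necessary" and defers full specification to an analysis plan to be approved before data collection ends. The Study design section sets three visits: "assessments at 6 weeks (baseline) and 4 and 7 months after hospital discharge".

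**The concern.** In their usual forms, a random intercept with independent residuals and a random intercept with autoregressive residuals share one restriction: the total variance is the same at each visit. A criterion that compares only these two cannot detect that the restriction is wrong, because both candidates carry it.

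Equal spread is doubtful for several outcomes here. SART errors, Hotel Task deviation time, DEX, CFQ, FAQ and PHQ-9 all have a floor at zero. They are followed through recovery from a 6-week visit at which the Discussion expects heavy opioid use and moderate to severe pain. Spread may shrink as patients improve, or grow as courses diverge. The standard error of a between-group difference at 7 months would then be too large or too small, and in which direction would vary by outcome.

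**Working it through.** **Inputs from the protocol.** Three visits; 1:1:1 allocation; "target of 90 participants (30 per group) with complete follow-up data on 72 (85 %) by the 7-month follow-up". The check uses 72/3 = 24 completers per arm. (72/90 is 80%, not 85%; this does not affect the standard-error ratios below.) Two-sided 0.05 is assumed.

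**Plan's own figure.** There is none to reproduce. The Sample size section gives no SDs, visit correlations or numerical power. All SD patterns and correlations below are assumptions.

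**Step 1: variance implied by each model.**
- Random intercept + independent residuals: Var = τ² + σ² at every visit.
- Random intercept + equal-variance AR(1): Cov(s,t) = τ² + σ²ρ^|s−t|, so again Var = τ² + σ² at every visit.
- With a random slope: Var(t) = τ₀² + 2tτ₀₁ + t²τ₁² + σ², which changes with time.

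**Step 2: error in the 7-month standard error.** With complete data and arm-by-visit means, the fitted common variance is the mean of the three true variances. So model SE / true SE is R = √[(s₁² + s₂² + s₃²)/3] / s₃, and coverage is 2Φ(1.96R) − 1. Numerical AR(1) fits, run for the relative patterns (those starting at 1), gave the same ratios to within 0.002. The slope column comes from large-sample likelihood fits: correlations 0.6 throughout or 0.65/0.5 for the relative patterns, and 0.6/0.5/0.7 for the others.

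| SDs at 6 wk, 4 mo, 7 mo | Mean variance | R, no slope | Coverage | R with random slope |
|---|---|---|---|---|
| 1, 1, 1 | 1.000 | 1.00 | 95.0% | 1.00–1.02 |
| 1, 1.1, 1.2 | 1.217 | 0.92 | 92.8% | 0.99–1.01 |
| 1, 1.15, 1.3 | 1.338 | 0.89 | 91.9% | 0.99–1.00 |
| 8, 9, 11 | 88.67 | 0.86 | 90.7% | 1.00 |
| 1, 1.25, 1.5 | 1.604 | 0.84 | 90.2% | 0.985–1.00 |
| 1, 0.9, 0.8 | 0.817 | 1.13 | 97.3% | 1.02–1.03 |
| 1, 0.85, 0.7 | 0.738 | 1.23 | 98.4% | 1.035–1.047 |
| 10, 8, 6 | 66.67 | 1.36 | 99.2% | about 1.09 |

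Example: √66.67 / 6 = 8.165/6 = 1.36. For 10-9-8, which has the same relative spread as 1, 0.9, 0.8, the slope fit with correlations 0.6/0.5/0.7 gives a standard error 4–5% too large.

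**Step 3: change from 6 weeks to 7 months.** Random intercept + AR(1) gives ratios of 0.98–1.00 over all patterns. Random intercept + independent gives 0.88–1.00. Most of that shortfall comes from correlation that decays over time, since it is 0.894 even with equal SDs and correlations 0.65/0.5.

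**Step 4: small-sample simulation.** 24 per arm, three arms, baseline-adjusted 7-month contrast, correlations 0.6/0.5/0.7, AIC in place of DIC. Ranges cover repeated runs; single values were available from one run only. The largest set used 2,500–4,000 trials per pattern and an effect of 0.826 residual SD.

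| SDs | Measure | Two stated structures | Slope added as candidate | Unstructured |
|---|---|---|---|---|
| 10-8-6 | type I error | about 1% | 3.4% | 5–6% |
| 10-8-6 | power | 50–54% | 69–73% | 78–81% |
| 10-9-8 | type I error | 3% | 3.7% | 5–5.5% |
| 10-9-8 | power | 74–75% | 71–78% | 81–82% |
| 8-9-11 | type I error | 8–11% | 4.4% | 4–6% |
| equal | power | 82–83% | 83% | 82–83% |

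In one run at 10-9-8, AIC chose the slope in 44% of trials when it was offered.

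**Step 5: cost of the unstructured fit.** It has 6 covariance parameters, against 2 (random intercept), 3 (with AR(1)) or 4 (with slope). At 24 per arm its mean 7-month standard error was 0.285, 0.374 and 0.202, against true values of 0.289, 0.375 and 0.202 for SDs 1/1/1, 1/1.15/1.3 and 1/0.85/0.7. Coverage was 94–97%. Under equal spread its standard error was more variable: SD 0.024 against 0.018, about one third more.

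**The case against.** A reader might infer that the plan forces equal variance at all visits, that the 7-month intervals are therefore wrong, and that an unstructured matrix costs nothing. The protocol does not support that reading.

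- **Equal variance is not built in.** The sentence before the quoted one permits a random slope, and the text does not say that the autoregressive form has equal variances. The large-sample slope fit removes the false-positive inflation at 8-9-11 (ratio 1.00). Its deviance there beats random intercept + AR(1) by about 10 at n = 72 for one extra parameter, so a criterion would be expected to favour it if it were offered. What remains with the slope is mainly a conservative error when spread falls.
- **The contrast matters.** The protocol does not fix a baseline-adjusted 7-month difference as the estimate of interest, and change from baseline under autoregressive errors is nearly immune.
- **The SD patterns are assumed.** Tower, Trails B and FAS are norm-referenced scores, so shrinkage towards zero does not apply to them. For skewed scores the plan already allows transformation or nonparametric methods, which may stabilise the spread.
- **The cost is not nil.** The simulations used complete balanced data, whereas dropout and multiple imputation are planned, and AIC stood in for DIC.
- **Covariance detail normally belongs in the analysis plan**, which the protocol promises.

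The first four points stand and limit the claim. The last is only half right: the protocol does more than leave the matter open, because it names the candidates and the selection rule. A later plan that follows it inherits the restriction. An optional slope with no trigger does not reliably repair it: even as a candidate, the slope left power below the unstructured fit in both falling-spread cases.

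**Conclusion.** The point holds in conditional form. If no slope is fitted and the autoregressive structure has equal variances, and if spread changes during recovery, the standard error of the 7-month group difference is about 13–36% too large for an SD fall of 20–40%, or about 8–16% too small for a rise of 20–50%. At 8-9-11, the rising pattern simulated, type I error was about 8–11% instead of 5%. The conclusion rests on assumed visit SDs and correlations, complete data and AIC for DIC. It concerns the 7-month difference, much less the change from baseline, and a selected slope removes most of the error. This is a cheap improvement to a workable method; it does not make the planned analysis invalid.

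**What to change.** In the analysis plan, for outcomes analysed with the longitudinal model, replace the criterion-based choice with one prespecified model: visit as a category, arm-by-visit terms, an unstructured 3×3 within-patient covariance and small-sample degrees of freedom. The unstructured matrix takes the place of the random intercept, because the two cannot be identified together. Name a fallback with visit-specific variances for non-convergence. Keep the random-intercept, random-slope and autoregressive fits as sensitivity analyses.

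The cost is a short change of text, which is still possible because the Trial status section places the study in follow-up and the analysis plan is due before data collection ends. It adds three or four covariance parameters to the two stated structures and makes the standard error somewhat more variable. No power loss was measurable under equal spread.

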### Ethics

Ethical approval has been received from Vanderbilt Institutional Review Board (IRB# 111484) at the participating center and prospectively registered at www.ClinicalTrials.gov (NCT01714531).

## Discussion

The proposed study will focus on a patient population that has significant yet clinically unrecognized and unmanaged cognitive impairment in the vital domain of executive functioning. Assessment and treatment of cognitive impairment in trauma survivors at Level I trauma centers is currently limited to patients with moderate to severe TBI. We propose to identify patients with mild TBI and clinically significant impairment in executive functioning and implement a targeted evidence-based cognitive rehabilitation program. Since previous investigations have suggested that deficits in executive functioning may contribute to the development and maintenance of depression and PTSD [17, 18], our intervention also has the potential to ameliorate depressive and PTSD symptoms during the first year of recovery following major trauma. Innovative rehabilitation interventions such as our GMT program have the potential to address poor return to work rates and profound functional and psychological disability noted in trauma survivors with mild TBI.

This study will have a direct impact on traditional rehabilitation practice. Our interventional approach broadens the availability of evidence-based cognitive strategies by expanding implementation from traditional providers, such as occupational therapists, speech-language pathologists, and neuropsychologists, to physical therapists. Compelling data are needed to support the expanding role of the physical therapist in integrating cognitive and functional strategies into patient management. This is especially important since trauma survivors are commonly referred to physical therapists during the early recovery period to address physical impairments and disability. Physical therapists are in a unique position to assess and manage both the physical and cognitive consequences of injury.

Our cognitive rehabilitation intervention will also serve to accelerate a telephone-delivery approach to rehabilitation services. Teletherapy has been used effectively in adults with chronic medical conditions and depression [65–68]. In patients with brain injury, Salazar and colleagues [69] found no significant differences in outcomes between in-hospital and telephone-based cognitive rehabilitation in military personnel with moderate to severe closed head injury. Additional research is needed to overcome common perceptions that visual contact is necessary for effective treatment. Telephone-based rehabilitation appears to be a promising approach to service delivery in patients with cognitive deficits and multiple barriers to effective treatment (that is, insurance and transportation limitations, work instability, and lack of social support and community resources). The proposed study extends the telephone-delivery model in order to improve the accessibility of effective cognitive strategies for trauma survivors.

We anticipate several difficulties in implementing the study protocol. First, the cognitive tests are time intensive and require in-person visits, which may negatively affect patient enrollment and retention. Second, we anticipate patients having a lack of awareness regarding cognitive deficits. This diminished understanding of the need for cognitive rehabilitation may impact enrollment as well as engagement in the study programs. Third, we also anticipate that completing the in-person screening and baseline assessment during the first 6 weeks following hospital discharge may be difficult due to high levels of opioid use, moderate to severe pain levels, injury to the hand or arm, and financial and geographic constraints. However, we were interested in testing our interventional approach during the early postoperative period. The National Academy of Sciences Committee on Cognitive Rehabilitation Therapy for Traumatic Brain Injury recommends that further research is needed to test the efficacy of cognitive rehabilitation therapy in individuals with milder injuries and during the subacute phase [20].

A limitation of the design of this study includes the 7-month follow-up, which impacts the ability to assess sustainability of study results. However, the priority was having adequate statistical power to detect efficacy rather than longitudinal follow-up. Serial neuropsychological assessments can result in practice effects and this will be addressed methodologically using the Reliable Change Index [13]. A potential limitation of a longitudinal study in trauma survivors is that intervening events could affect outcomes. Therefore, an intervening events questionnaire will be used to track rehospitalization, additional surgery, complications, and new or continuing use of opioid or psychoactive medications. We will use these data to control for effects of intervening events on outcomes across groups. Finally, dose–response is an important issue for the proposed study. Secondary analyses to examine the number of sessions completed will begin to explore the dose–response relationship. A next step will be to conduct a multicenter trial to further validate the telephone-based GMT intervention and improve generalizability of findings.

This study will be the first to investigate systematically a physical therapist-delivered, telephone-based cognitive rehabilitation program in patients with mild head injuries. Innovative rehabilitation interventions and delivery methods are needed to improve outcomes in trauma survivors with significant yet unrecognized cognitive impairment. Early interventional studies are also needed to address the moderate to severe cognitive, physical, and emotional impairments associated with mild TBI, especially cognitive deficits in executive functioning. There are currently no standards of treatment and early assessment and management of mild TBI are critical for optimal recovery. Overall, this line of work has the potential to benefit a large population of trauma survivors by enhancing their ability to return to a productive life both inside and outside the home.

## Trial status

Recruitment was completed in February 2015. This study is currently in the follow-up phase.

## Abbreviations

CDC: Centers for Disease Control
CFQ: Cognitive Failures Questionnaire
DEX: Dysexecutive Questionnaire
D-KEFS: Delis-Kaplan Executive Function System
FAQ: Functional Activities Questionnaire
GMT: Goal Management Training
IADL: instrumental activities of daily living
NIDDR: National Institute on Disability and Rehabilitation Research
PI: principal investigator
PCL-C: PTSD Checklist-Civilian Version
PHQ-9: Patient Health Questionnaire
PTSD: posttraumatic stress disorder
QOLIBRI-OS: Quality of Life after Brain Injury Overall Scale
SART: Sustained Attention to Response Test
SD: standard deviation
TBI: traumatic brain injury
